### Outcome measures

#### Primary outcomes

Primary outcomes will include self-reported measures of affect, appraisals of task-related stress, trait and state rumination, as well as trait and state self-compassion. Further primary outcomes will be response and habituation indices of biological stress measures for HPA axis, autonomic, and inflammatory responses (i.e., cortisol, sAA, HR, HRV, plasma IL-6, cytokine expression rates of IL-6, IL-1β, NF-кB, IкB). To obtain response indices, delta scores will be computed for the initial and repeated exposure to stress using peak values relative to baseline (e.g., peak cortisol values at + 1, + 10, or + 20 min post-TSST minus cortisol values at –1 min pre-TSST). To obtain habituation indices of biological stress measures, values of the second stress response will be subtracted from the first stress response values.

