Hypothesis 5: Independent of experimental session and group, stress elicits significant responses of biological stress system activity.Hypothesis 6: At experimental session 1, responses of biological stress system activity will be indifferent between participants from intervention groups 1 (rumination) and 2 (self-compassion) as well as participants from the control group (no intervention).Hypothesis 7: At experimental session 2, responses of biological stress system activity will be strongest in participants from intervention group 1 (rumination) and lowest in participants from intervention group 2 (self-compassion).Hypothesis 8: Habituation of biological stress system activity will be lowest in participants from intervention group 1 (rumination) and strongest in participants from intervention group 2 (self-compassion).Hypothesis 9: Self-compassion and positive affect will predict lower biological responses to repeated stress, whereas rumination, negative affect, and stress appraisals will predict higher biological responses to repeated stress.Hypothesis 10: Self-compassion and positive affect will predict stronger habituation of biological stress system activity to repeated stress, whereas rumination, negative affect, and stress appraisals will predict lower habituation of biological stress system activity to repeated stress.

We expect these changes to occur among markers of the HPA axis, the autonomic system, as well as the inflammatory system.

Associations of biological stress system activity with other psychological variables (e.g., emotion regulation, coping) as well as demographic (e.g., age, gender, sex) and anthropometric (e.g., BMI) variables will be tested in an exploratory fashion.

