### Data preparation and statistical analysis

Data preparation and statistical analysis will be performed using IBM SPSS Statistics 26 (IBM Corp., Armonk, NY, USA). Following our pre-registered analysis plan [60], data will be screened for outliers using *z*-scores, and outliers which differ more than 3 standard deviations from the participants’ mean will be excluded from further analysis. In addition, participants will be excluded in case of elevated cortisol levels (e.g., > 12 nmol/L or *z* > 3.29) after arrival at the laboratory (i.e., at baseline) and after accommodating to the testing situation (i.e., at − 1 min relative to the TSST). Additionally, non-adherent participants whose missing values exceed 25% of the data will also be excluded from the analysis. In the next step, Kolmogorov–Smirnov tests will be conducted in order to check for normal distribution. If necessary, data will be log-, ln-, or inverse transformed to reduce skewness of biological data.

To analyze the data (i.e., to compare self-report measures as well as biological response and habituation indices between experimental groups), we will use separate analyses of covariance (ANCOVAs). Sex and BMI will be used as covariates in analyses of biological data, as these two variables have been repeatedly shown to be highly relevant for stress system activity [61, 62]. We will use the standard *p* < 0.05 criteria for determining if the ANCOVA and the post hoc test suggest that the results are significantly different from those expected if the null hypothesis were correct. The post-hoc Bonferroni test adjusts for multiple comparisons.

To investigate associations between primary psychological outcome measures and indices of biological stress measures, we will compute separate hierarchical linear regression models, regressing biological outcome measures onto psychological outcome variables. Again, sex and BMI will be included as covariates in these analyses. When examining state variables, the respective trait variable will be included as covariate in regression analyses.

We expect that certain psychological (e.g., emotion regulation, coping), demographic (e.g., age, gender, sex), and anthropometric (e.g., BMI) variables may be related to biological stress system activity. Therefore, we will test for relationships between these variables and primary outcome measures of biological stress responses in an exploratory fashion.

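### The ANCOVAs for Hypotheses 7 and 8 leave out the session-1 response as a covariate, which costs precision and lets a chance session-1 imbalance pull the two tests in opposite directions

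*Protocol article*

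**What the plan says.** Under Primary outcomes, the protocol builds a response index for each session: "delta scores will be computed for the initial and repeated exposure to stress using peak values relative to baseline". It then forms the habituation index: "values of the second stress response will be subtracted from the first stress response values".

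Two hypotheses compare the arms after the intervention. Hypothesis 7 reads "At experimental session 2, responses of biological stress system activity will be strongest in participants from intervention group 1 (rumination) and lowest" in the self-compassion arm. Hypothesis 8 reads "Habituation of biological stress system activity will be lowest in participants from intervention group 1 (rumination) and strongest" in the self-compassion arm.

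Under Data preparation and statistical analysis, separate ANCOVAs are planned "to compare self-report measures as well as biological response and habituation indices between experimental groups". On adjustment, the text says "Sex and BMI will be used as covariates in analyses of biological data". The only other adjustment named is the matching trait variable, and that belongs to the regressions on psychological state variables, not to the group comparisons.

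Randomisation is stratified for sex alone (Randomization), so the design does not balance the session-1 response. Hypothesis 6 nevertheless expects it to be equal: "At experimental session 1, responses of biological stress system activity will be indifferent between participants".

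**The concern.** Call the session-1 and session-2 response indices R1 and R2. If R1 is complete before the intervention, randomisation makes its expected value the same in all arms. Hypothesis 7 (R2) and Hypothesis 8 (R1 - R2) then estimate the same treatment effect with opposite sign. The raw comparison fixes the slope on R1 at 0 and the difference score fixes it at 1. An ANCOVA with R1 as covariate estimates the slope from the data.

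Two things are at stake. The first is precision on the trial's central question. The second is interpretation: both indices are primary outcomes, and an arm that happens to start high in session 1 is moved one way on Hypothesis 7 and the other way on Hypothesis 8. The two answers can then differ without any substantive reason.

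**Working it through.** **Inputs from the protocol.** Three groups, 1:1:1, alpha 0.05, power 0.80, N = 111 (37 per arm), planned total 120, anticipated dropout 10%. The effect size is printed as f² = 0.30. The planning effects (d = 0.81 for cortisol, 0.67 for sAA) are differences in habituation.

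**Assumptions.** The correlation rho between R1 and R2 is not given; 0.3, 0.5 and 0.7 are used. The response SD is set to 1 in both sessions.

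**Step 1: reproduce the plan's figure.** Noncentral F with noncentrality f²N, df1 = 2, df2 = N - 3 - number of covariates. With f = 0.30 and N = 111, the noncentrality is 0.09 × 111 = 9.99 and power is 0.803, with 0 or with 2 covariates. Taken literally, f² = 0.30 (f = 0.548) would need only N = 36. The stated 111 therefore reproduces only if 0.30 is Cohen's f, and that reading is used below for the habituation index.

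**Step 2: residual variances and effect sizes.**
- Hypothesis 8, unadjusted: Var(R1 - R2) = 2(1 - rho), with f = 0.30 by assumption.
- Hypothesis 7, unadjusted: Var(R2) = 1, so f = 0.30 × sqrt(2(1 - rho)).
- Adjusted for R1: variance 1 - rho², so f = 0.30 × sqrt(2/(1 + rho)).

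| | rho 0.3 | rho 0.5 | rho 0.7 |
|---|---|---|---|
| Variance: H8 / H7 / adjusted | 1.4 / 1 / 0.91 | 1.0 / 1 / 0.75 | 0.6 / 1 / 0.51 |
| f: H8 / H7 / adjusted | 0.300 / 0.355 / 0.372 | 0.300 / 0.300 / 0.346 | 0.300 / 0.232 / 0.325 |
| Power at N = 111, H8 unadjusted | 0.803 | 0.803 | 0.803 |
| Power at N = 111, H7 unadjusted | 0.920 | 0.803 | 0.571 |
| Power at N = 111, adjusted | 0.943 | 0.907 | 0.866 |
| N for 80% power, adjusted | 75 | 84 | 96 |

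With 10% loss from 120 (0.9 × 120 = 108), the powers are 0.791 for H8, 0.913 / 0.791 / 0.558 for H7 and 0.937 / 0.898 / 0.856 adjusted.

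**Step 3: effect of a chance imbalance.** Suppose the self-compassion arm has a mean R1 higher by D. Its expected R2 is higher by rho*D, which counts against Hypothesis 7. Its expected habituation index is higher by D - rho*D = (1 - rho)*D, which counts in favour of Hypothesis 8. If the rumination arm starts high, the signs reverse: Hypothesis 7 is favoured and Hypothesis 8 disfavoured. One standard error of the R1 difference between two arms of 37 is sqrt(2/37) = 0.232 SD. An imbalance of that size shifts the R2 contrast by 0.070 / 0.116 / 0.163 SD and the habituation contrast by 0.163 / 0.116 / 0.070 SD at rho 0.3 / 0.5 / 0.7. In simulation (5,000 trials per setting, 37 per arm) the slopes on the imbalance matched these values, and they were about 0 after adjustment.

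**Step 4: disagreement between the tests.** With the assumed effect, unadjusted Hypotheses 7 and 8 differed on significance in 18% / 25% / 39% of simulated trials.

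**Step 5: the adjusted tests coincide.** Since R1 - R2 is the outcome and R1 is in the model, the group coefficients are those of the R2 model with the sign changed, and the residuals change sign only. The F statistic is therefore the same. Simulated p-values agreed to within 1e-13.

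**The case against.** Several objections have force.

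- **Validity.** A reader might infer that the planned tests are invalid. They are not. Both are unbiased over randomisations, and with no effect each rejected in 4.7% to 5.2% of simulated trials. What remains is lost precision and bias conditional on the observed imbalance.
- **Power target.** A reader might infer that Hypothesis 8 misses its target. On the f = 0.30 reading it has the intended 80% at N = 111, because the planning effects are habituation differences. The gain is also uneven: at rho 0.3, Hypothesis 7 rises only from 0.92 to 0.94. A real shortfall appears only for Hypothesis 7 at rho above 0.5.
- **Cause of disagreement.** Not all of it comes from imbalance. At rho 0.7 much of the 39% arises because one test has 57% power and the other 80%.
- **Timing.** A reader might infer that the session-1 response precedes the intervention for every marker. The document does not show this. The abstract puts assignment directly after the first stress test, and the procedure section gives no minute for the writing task. Session-1 saliva runs to +45 min, and blood is drawn at +30 and at +90 (Table 2) or +120 min (Experimental setting and procedure). For plasma IL-6 and the four expression markers, R1 may be partly post-task, and adjusting for it could remove part of the effect. This objection stands and limits the fix.
- **Strength of the covariate.** No between-session correlation is reported, so nothing shows R1 to be the best predictor available. The gain for Hypothesis 8 nevertheless holds at any rho below 1, and for Hypothesis 7 at any rho other than 0, apart from one degree of freedom.
- **The pre-registered plan.** It is cited but not shown, and it may hold a rule for conflicting results, so the absence of one cannot be asserted. The covariate list, however, is stated in the article itself.

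**Conclusion.** The point holds as one of efficiency and conditional bias, not of an invalid analysis. As written, the group comparisons adjust for sex and BMI and leave the session-1 response unused. Under equal SDs, rho of 0.3 / 0.5 / 0.7 and f = 0.30 on the habituation scale, adjustment raises power at N = 111 from 0.80 to 0.94 / 0.91 / 0.87 for Hypothesis 8, and from 0.92 / 0.80 / 0.57 to the same values for Hypothesis 7. The opposite-direction shift requires 0 < rho < 1 and similar SDs in the two sessions. The conclusion is firm for HR and HRV during the stress test. It is firm for cortisol and sAA if the peak samples precede the writing task. It is conditional for the five inflammatory markers until the timing of that task is stated.

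**What to change.** In Data preparation and statistical analysis:

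1. For each marker whose session-1 response is complete before the writing task, add that marker's session-1 response index as a covariate, with sex and BMI, in the ANCOVAs of the session-2 response and the habituation index. Use the same scale and transformation for the covariate as for the R1 inside the index; otherwise the two models no longer coincide.
2. For those markers, report one treatment test. The habituation wording can stay.
3. State when the writing task starts relative to the session-1 samples, and reconcile the +90 and +120 min blood times. If R1 for plasma IL-6 or the expression markers is partly post-task, adjust only for a pre-task session-1 value, such as the -1 min sample where it is on a usable scale, and do not present Hypotheses 7 and 8 as the same test. For expression, values normalised to a -1 min baseline within each session would leave that sample with no variation, so an un-normalised value would be needed.

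The cost is one sentence (plus the timing statement) and one degree of freedom, with no new data. The protocol plans no analysis before data collection ends, so the change can be fixed in advance.

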## Methods

### Study design

The study is designed as a randomized controlled, single-center, and single-blinded trial, in which participants will be randomly assigned to one of two intervention groups (rumination vs. self-compassion) or a control condition (see “Randomization”) with an allocation ratio of 1:1:1. The study employs a superiority trial design, aiming to determine whether one of the two cognitive coping interventions is more effective in modifying the responsiveness and habituation of biological stress systems compared to the control condition. The design encompasses repeated measurements of each group, i.e., each group will undergo two experimental sessions (t1 and t2) comprising stress test exposures, and within each experimental session, repeated biological and psychological outcome assessments will take place (see Table 1).

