### Power analysis

An a priori power analysis has been conducted using G*Power (version 3.1.9.6) for sample size estimation, based on the findings of a preliminary study [20]. The analysis is limited to the reference biomarkers cortisol and sAA, as no available data provide insights into the modifiability of inflammatory response patterns.

As demonstrated in the aforementioned preliminary study [20], the findings suggest a high modifiability of cortisol and sAA responses through the manipulation of psychological coping mechanisms. Specifically, a large effect was observed in the difference in cortisol response habituation between intervention and control group (*d* = 0.81), while a moderate-to-large effect was found for the difference in sAA response habituation (*d* = 0.67). Based on these findings, medium-to-large effects are expected for differences between experimental groups with regard to their difference in habituation of biological stress system activity. Power analyses revealed a sample size of *N* = 111 (*n* = 37), using an effect size of *f*^2^ = 0.30, *α* = 0.05, 1-*β* = 0.80, number of groups = 3. To address the anticipated 10% dropout rate caused by non-appearance of participants on study day 2 or insufficient biological sample volumes, an additional nine participants (three per condition) will be recruited and tested in this study, resulting in a total sample size of *N* = 120.

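### With exactly three arms, the Bonferroni step is valid but needlessly conservative; a Shaffer step-down gives the same 5% guarantee per outcome with more power, mainly for the comparisons with control

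*Protocol article*

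**What the plan says.** Under Study design, participants are "randomly assigned to one of two intervention groups (rumination vs. self-compassion) or a control condition", "with an allocation ratio of 1:1:1". Under Data preparation and statistical analysis, each outcome gets its own ANCOVA, and for the biological outcomes "Sex and BMI will be used as covariates in analyses of biological data". The significance rule reads in part "We will use the standard *p* < 0.05 criteria for determining if the ANCOVA and the post hoc test suggest", followed by "The post-hoc Bonferroni test adjusts for multiple comparisons".

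Two things are not stated there: how many comparisons form the Bonferroni family, and whether the post hoc tests are run only after a significant ANCOVA. The section refers to a pre-registered analysis plan, which is not at hand and may settle both.

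Under Power analysis, the trial is sized on a three-group test ("number of groups = 3") at alpha 0.05 and 80% power, giving 111 participants, 37 per arm. No power is given for a pairwise comparison. The preliminary effects quoted there are d = 0.81 (cortisol habituation) and d = 0.67 (sAA habituation), intervention versus control.

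**The concern.** The scientific claims rest on pairs of arms. Study design frames superiority as an intervention against control. Hypotheses 7 and 8 place rumination and self-compassion at opposite ends, which puts control between them. A significant three-group test alone does not show which arm moved.

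With three means, the pairwise null hypotheses are logically linked: if any two pairs are equal, all three are. Bonferroni ignores this link and holds every pair to 0.0167, even after one difference has been established. At stake is the chance of detecting real differences from control in a trial whose sample size was set for the omnibus test only.

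**Working it through.** **Inputs.** From the article: three arms, 1:1:1, 37 evaluable per arm, alpha 0.05, effects 0.67 and 0.81 SD, covariates sex and BMI (error df = 111 − 5 = 106). Assumed: the family is the three pairs; errors are normal with equal variance; 0.5 SD stands for the lower end of the medium-to-large range that the article gives in words only.

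**The plan's own figure.** For a three-group F test, noncentrality = N·f², with df 2 and N − 3. With f = 0.30, N = 108 gives power 0.792 and N = 111 gives 0.803, so the stated 111 is reproduced. The article prints "using an effect size of *f*^2^ = 0.30"; read literally as f², N = 36 would already give 0.809. I therefore use f = 0.30. Equally spaced means (−d, 0, +d) have f² = 2d²/3, so f = 0.30 corresponds to d = 0.30 × √1.5 = 0.367 SD.

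**Why the step-down holds 5%.** Test the smallest p-value at 0.05/3; if it is significant, test the other two pairs at 0.05.
- All three arms equal: an error requires the smallest p-value to be at or below 0.05/3, which has probability at most 3 × 0.05/3 = 0.05.
- Exactly one pair equal: that pair can be rejected only if its p-value is at or below 0.05, so the error is at most 0.05.
- No pair equal: no false rejection is possible.

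Exactly two equal pairs cannot occur. Any pair with p at or below 0.0167 is always rejected, so nothing is lost relative to Bonferroni. No omnibus test is needed.

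**Direct check of the Bonferroni column.** Noncentral t with 106 df, noncentrality d·√(37/2), critical value 2.433 at 0.0167 (1.983 at 0.05). For d = 0.67 the noncentrality is 2.88 and power is 67.3% at 0.0167 and 81.5% at 0.05. For d = 0.5 it is 2.15, giving 39.3% and 56.8%.

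**Simulation** (one million trials per scenario, 37 per arm, 106 df). The last column is unadjusted pairs tested only after a significant omnibus F.

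| Scenario | Quantity | Bonferroni | Step-down | Gated, unadjusted |
|---|---|---|---|---|
| One arm apart by 0.67 SD | each true pair | 67.4% | 75.1% | 77.4% |
| | both true pairs | 52.7% | 68.2% | 70.3% |
| One arm apart by 0.81 SD | each true pair | 85.1% | 90.6% | 91.7% |
| Equally spaced, f = 0.30 | each pair with control | 20.2% | 33.0% | 33.8% |
| | widest pair | 76.6% | 78.0% | 79.6% |
| Equally spaced, 0.5 SD (assumed) | each pair with control | 39.3% | 56.6% | 56.7% |
| | widest pair | 96.8% | 97.1% | 97.4% |
| All arms equal | family-wise error | 4.4% | 4.4% | 5.0% |
| One pair equal, third arm 0.67 SD away | family-wise error | 1.7% | 4.9% | 5.0% |

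Step-down gains: 90.6 − 85.1 = 5.5 and 75.1 − 67.4 = 7.7 points with one arm apart; 33.0 − 20.2 = 12.8 and 56.6 − 39.3 = 17.3 points against control with equal spacing. For the widest pair the gains are 1.4 and 0.3 points (3.0 and 0.6 by the gated route).

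Unadjusted pairs with **no** gate have a family-wise error of about 12% when all arms are equal.

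**The case against.** The strongest case against raising this is that Bonferroni is a valid choice that nothing in the article contradicts, and that it comes with simultaneous confidence intervals. That stands: this is an efficiency point.

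A reader might infer that the plan pays twice for the same protection, because a significant ANCOVA is already required before the pairs are tested. The article does not say so; the term post hoc only suggests it. Without a gate, Bonferroni is the only protection within an outcome, and simply deleting it would allow about 12% error. The step-down does not depend on how this is resolved.

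A reader might also take a gain of this size to apply to every pairwise comparison. It does not. Rumination versus self-compassion, which Hypothesis 8 expects to be furthest apart, gains almost nothing. The upper end also rests on the assumed 0.5 SD, and the one-arm-apart scenarios set one intervention equal to control, which Hypothesis 8 does not predict.

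The unused error allowance is not worthless either. Primary outcomes lists nine biological measures plus self-report scales, and the analysis section states no correction across them. If all nine habituation indices had one equal pair and a differing third arm (an assumption), expected false pair claims would rise from about 9 × 0.017 = 0.15 to at most 9 × 0.05 = 0.45. This is a real cost, though Bonferroni within each outcome was not designed to control error across outcomes.

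Finally, Randomization says that the analyst knows the group assignments and relies on strict adherence to the pre-registered plan to limit bias. Relaxing a threshold during recruitment therefore has to be documented openly.

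**Conclusion.** This holds as a cheap improvement. The Bonferroni step is not an error, and the documents do not support calling it redundant after an omnibus gate. If the family is the three pairs, the step-down dominates it at the same 5% guarantee per outcome. At 37 per arm the benefit falls mainly on the comparisons with control. Even after the change, each of those has only about 33% power at the design effect with equal spacing. The guarantee follows from the logic of three means and needs only valid pairwise p-values; the power figures rest on the normal, equal-variance model and the assumed patterns of means.

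**What to change.** Replace the Bonferroni sentence with wording such as: *For each outcome the three pairwise comparisons are tested by Shaffer's step-down: the smallest p-value at 0.05/3 and, if it is significant, the remaining two at 0.05. Family-wise error is controlled at 5% within each outcome and not across outcomes.*

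The alternative is unadjusted pairs, but only with a strict gate written in: *Pairs are tested at 0.05 only if the omnibus ANCOVA for that outcome is significant at 0.05; otherwise no pair is declared different.*

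State that the family is the three pairs. Either keep Bonferroni-adjusted intervals, noting that they may include zero for a pair the step-down rejects, or report unadjusted intervals labelled as such. Record the change as a dated amendment to the pre-registered plan before any data are analysed; Status and timeline of the study rules out analyses before data collection ends, so this is still possible.

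The cost is one sentence, the amendment, and a step-down read from the three unadjusted p-values. No participants are added. The downsides are the loss of matching simultaneous intervals and fuller use of the 5% in each outcome.

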### Hypotheses

By increasing either ruminative or self-compassionate thoughts among healthy young adults, the intervention programs are expected to affect the regulation of occurring emotions as expressed by the responsiveness of biological systems during repeated stress exposure.

To check whether the experimental manipulations are successful on a psychological level, self-report measures will be assessed repeatedly over the course of each experimental session and are expected to change over the course of experimental sessions 1 and 2. Specifically, we hypothesize that stress will elicit changes in affect scores and stress appraisals, whereas the two intervention programs are expected to induce changes in affect, self-compassion and rumination, which will be stronger than in the control group (no intervention). Furthermore, we expect these variables to predict indicators of biological stress system activity.

Hypothesis 1: Independent of experimental session and group, stress will elicit significant increases of negative affect and stress appraisals as well as decreases of positive affect.Hypothesis 2: At experimental session 1, stress-induced changes of positive and negative affect and stress appraisals will be indifferent between participants from intervention groups 1 (rumination) and 2 (self-compassion) as well as participants from the control group (no intervention).Hypothesis 3: At experimental session 2, stress-induced decreases of positive affect as well as increases of negative affect and stress appraisals will be strongest in participants from intervention group 1 (rumination) and lowest in participants from intervention group 2 (self-compassion).Hypothesis 4: Increases in state self-compassion and positive affect from pre- to post-intervention will be strongest in intervention group 2 (self-compassion), and increases in state rumination and negative affect will be strongest in intervention group 1 (rumination).

Furthermore, we expect significant responses of biological stress system activity in all experimental groups at each experimental session. Specifically, we expect responses of biological stress system activity to be similar at experimental session 1 and participants from intervention group 2 (self-compassion) to show stronger habituation of stress system activity compared to intervention group 1 (rumination) or the control group (no intervention).

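### For predictors measured after the intervention, the Hypothesis 9 and 10 regressions leave out randomised group, so a significant coefficient may only restate the group differences

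*Protocol article*

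**What the plan says.** The section on data preparation and statistical analysis describes separate hierarchical linear regressions, "regressing biological outcome measures onto psychological outcome variables". It names the adjustment set: "Again, sex and BMI will be included as covariates in these analyses". It adds a conditional covariate: "When examining state variables, the respective trait variable will be included as covariate in regression analyses". Neither randomised group nor a fit within arms is mentioned.

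The hypotheses served are worded across all participants. Hypothesis 9 begins "Self-compassion and positive affect will predict lower biological responses to repeated stress", and Hypothesis 10 begins "Self-compassion and positive affect will predict stronger habituation of biological stress system activity to repeated stress"; both continue with the opposite direction for rumination, negative affect and stress appraisals.

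The same section expects the arm to move both sides of these regressions:

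- **Predictors.** Hypothesis 4 orders the pre-to-post-intervention changes in state self-compassion, state rumination and affect by group. Hypothesis 3 does the same for session 2 affect and stress appraisals.
- **Outcomes.** Hypotheses 7 and 8 order session 2 biological responses and habituation by group, with rumination and self-compassion at opposite ends.

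**The concern.** On the protocol's own hypotheses, the randomised arm is a cause of the predictor and a cause of the outcome. When three arms are pooled and both have shifted, the points line up along the arm means even if the two measures are unrelated within each arm. The listed covariates cannot remove this. Sex, BMI and the screening trait scores are fixed before the intervention and, apart from chance, do not differ between arms.

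If Hypotheses 4 and 8 hold, Hypothesis 10 may then come out significant for that reason alone, and likewise Hypothesis 9 if Hypotheses 3 or 4 and 7 hold. A reader of the results could count such a finding as further support for a psychological–biological link when it repeats the group comparison. The randomised comparisons themselves are not touched.

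**Working it through.** **Inputs from the protocol**

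- Three arms, 1:1:1, α = 0.05.
- 120 recruited with 10% dropout expected: 120 × 0.90 = 108 analysed.
- Sizing: N = 111 at 80% power. A noncentral F calculation reproduces 111 (power 0.803) with f = 0.30. The article prints the value as f², but f² = 0.30 read literally would need only 36. I use f = 0.30, the reading that gives the stated N. This sizing concerns the group comparison; the article gives no figure for the regressions.
- Preliminary habituation effects: d = 0.81 (cortisol) and d = 0.67 (sAA), intervention against control.

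**Assumptions, not in the documents**

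- Arms equally spaced (rumination, control, self-compassion), with step a in the predictor and step b in the outcome, both in within-arm SDs.
- a = 0.5 to 1.0. For b, the upper value follows from f = b × √(2/3), so b = 0.30/0.816 = 0.37. The lower value, 0.25, is a smaller effect chosen for range.
- No association within any arm.

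**Induced correlation.** Arm scores −1, 0, +1 have variance 2/3, so

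r = (2/3)ab / √[(1 + (2/3)a²)(1 + (2/3)b²)]

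- Smallest: 0.0833 / √(1.1667 × 1.0417) = 0.076.
- Largest: 0.2467 / √(1.6667 × 1.0913) = 0.183.

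**Chance of p < 0.05.** Fisher's z has mean atanh(r) × √(108 − 3) = atanh(r) × 10.25 and SD 1.

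| a | b | r | mean z | pooled p < 0.05 |
|---|---|---|---|---|
| 0.5 | 0.25 | 0.076 | 0.78 | 12% |
| 0.5 | 0.37 | 0.109 | 1.12 | 20% |
| 1.0 | 0.25 | 0.126 | 1.30 | 26% |
| 1.0 | 0.37 | 0.183 | 1.90 | 47% |

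Simulation of the same four settings (4000 trials each, N = 108) gave 13%, 20%, 26% and 49% pooled, and 4.6% to 5.4% with two group indicators.

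**With the planned covariates.** A second simulation (4000 trials per setting, 3 × 37) fitted sex, BMI, trait and state predictor, assuming a trait–state correlation of 0.5. Here d is the gap between the two extreme arms.

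| d on predictor | d on outcome | model as written | with group |
|---|---|---|---|
| 0 | 0 | 5.2% | 4.7% |
| 0.80 | 0 | 5.3% | 4.9% |
| 0 | 0.80 | 5.2% | 5.1% |
| 0.50 | 0.50 | 7.4% | 5.5% |
| 0.67 | 0.67 | 13.4% | 5.3% |
| 0.81 | 0.81 | 21.3% | 4.7% |
| 1.34 | 1.34 | 79.0% | 4.8% |
| 1.62 | 1.62 | 96.2% | 5.9% |

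Adjusting for trait does not protect. It removes within-arm noise from the predictor and leaves the arm difference in place. A check at d = 0.81: step 0.405, (2/3) × 0.405² = 0.109, partial r = 0.109/√(0.859 × 1.109) = 0.112, mean z = 0.1125 × √105 = 1.15, giving 21%.

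The last two rows apply only if each active arm differs from control by the preliminary d, in opposite directions, and the predictor moves as much.

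**The case against.** **The stated aim is association.** The analysis section says these models investigate associations, and the hypotheses say predict. A reader might infer that the protocol presents Hypotheses 9 and 10 as its test of mediation. It does not: the introduction tests the coping mechanism through the manipulation, and the strengths section credits the two conditions, the control and randomisation. As an association, the pooled coefficient is real in this sample, and 12% to 47% is not an error rate for it. This stands. The figures are error rates only for a claim of a link beyond the group differences.

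**Not every regression is affected.** A reader might infer that all the Hypothesis 9 and 10 models are compromised. Trait rumination and trait self-compassion come from screening, and some session 1 measures precede the intervention. Randomisation balances these.

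**Adjustment changes the question.** If a state measure truly carries the arm effect, conditioning on group removes the variation that the experiment created. The adjusted coefficient is not causal either, since the state measure is not randomised within arms. This stands too, and argues for reporting both coefficients.

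**The size is assumed.** No document gives the arm effect on the state measures, and the risks section allows that the interventions may be too short. With an extreme-arm gap of 0.50 on both variables the rate is only 7.4%.

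**The article is condensed.** The pre-registered analysis plan is not shown and may include group, and the contents of the hierarchical blocks are not given. But the article does list the covariates, down to a conditional one, and group is not on the list.

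**Conclusion.** The point holds for predictors measured after the intervention: post-intervention and session 2 state rumination, state self-compassion, affect and stress appraisals. For these, the listed covariates leave the arm as a common cause of predictor and outcome whenever the protocol's own hypotheses are right about both.

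With no within-arm association and 108 participants, the pooled coefficient is significant in about 12% to 47% of trials, with induced correlations of 0.08 to 0.18. With group in the model the rate is about 5%. The range rests on the assumed predictor steps, on equally spaced arms and on an outcome effect no larger than the planning value. It falls to about 5% if the arm moves only one of the two.

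The documents do not support saying that the pooled association is false, or that the group-adjusted coefficient alone should decide Hypotheses 9 and 10. What fails is reading a significant pooled coefficient as evidence separate from the group comparisons. This is a cheap improvement to the secondary inference, not a threat to the randomised results.

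**What to change.** For each Hypothesis 9 and 10 model whose predictor is measured after the intervention, add two group indicators as a separate block of the hierarchical regression, and report the psychological coefficient before and after that block. Describe the pooled coefficient as an association that includes the arm effect. Claim a psychological–biological link beyond the group differences only if the group-adjusted coefficient supports it. Models with trait scores or pre-intervention session 1 measures as predictors can stay as they are.

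If the pre-registered plan already includes group, it is enough to bring the article's covariate list into line with it.

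The cost is two degrees of freedom per model and one more row in the results; no new data are needed. The adjusted coefficient reflects only within-arm variation, so a null result there does not rule out mediation, and the report should say so. The article schedules all analysis after data collection and plans no preliminary analyses, so the change can be recorded before any result is seen. That matters because the analyst knows the allocation.
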